#### Women’s experiences

*Quantitative methods*. Pre-post intervention assessments will gather information on women’s experiences of SDMC at health facilities, and suffering of postpartum depression within 42 days of childbirth. Unlike health system assessment, two independent group of women will be enrolled in baseline and endline. Recently published structured questionnaire on mistreatment during childbirth will be contextually adapted and used for these pre-post assessments [33]. Postpartum depression and anxiety will be assesed using Patient Health Questionnaire– 9 and Generalised Anxiety Disorder– 7, respectively.

*Sample size calculation*. In order to get a sense of sample size requirement for a meaningful change study outcomes, the sample size was estimated with varied effect sizes. Mean score mistreatment was considered as key outcomes which is taken from a background study in similar setting that yielded a mean score of 25 (score range 0 to 40). A total of 308 postpartum women will be required to detect a statistical difference of 2.5-units decrease (or 10% reduction) in the mean score of mistreatment (from 25 [34] to 22.5) with standard deviation of 6 [34], 90% power, 5% level of significance, 2 design effect, and 10% lost-to-follow-up (LTFU) and/or non-response. We decided to proceed with a sample of 308 as it gives sufficient precision to perform range of additional analysis such as estimation of prevalence of different types of mistreatment and the effect of intervention on each of these types of mistreatment, while will not negatively affecting study timelines.

*Sampling strategy*. A convenience sampling technique will be used for the selection of study participants. All women giving births at the selected hospitals during the data collection period will be invited to participate in the survey, until the desired sample is achieved. The volume of women attending each health facility for childbirth may vary; hence based on historical trends the sample size will be proportionally distributed across health facilities according to the caseload. During the consent process, participants will be informed and asked whether they would be interested in participating in a follow-up interview in their homes at six weeks of postpartum. Women who showed interest in home-based interview and gave consent will be recruited in the survey. Participants who lived outside of the study district or even in hard-to-reach rural areas of the district will be excluded from this sample due to logistical constraints.

*Data collection and management*. Standardised and contextually-adapted tools will be used in this study. All data collection tools will be translated in the relevant local language and pre-tested in similar settings prior to being used. Data collectors with prior experience will be hired and trained for baseline and endline assessments, and routine audits. In-depth interviews (IDIs) and focus group discussions (FGDs) will be conducted by trained sociologist and/or anthropologist. All data collectors will receive a comprehensive and standardised training on both theoretical and practical aspect of study instruments. In addition, data collectors will be trained on rapport building, research ethics, and interviewing techniques. Research Officer will conduct: shadow interviews (observation of data collection) and independent re-interview/assessment with a sub-sample to ensure data quality.

Qualitative interviews will be audio-recorded for later transcription and translation. All quantitative data will be collected electronically on tablets. The software application, developed in Epicollect5, will have built-in validation checks to minimize data collection and entry errors. All software applications will be tested prior to their use in the study. Unique IDs will be given to each study participant which will be consistent (where applicable) in across assessments for synchronisation. Data Management person, under the supervision of study Co-Investigator will be responsible to manage all data that include: timely transfer to central database, data quality through routine assessments; data confidentiality, security, back-up, and sharing while maintaining anonymity. Study Investigators will coordinate closely with research officer and data collectors to ensure timely remedial measures.

*Data analysis*. Descriptive statistics will be used to describe the characteristics of study participants such as age, level of education, socio-economic status etc. In order observed change in women’s experiences of SDMC, advanced statistical techniques will be used to estimate changes in outcome indicators (SDMC experience) by means of multivariable linear (continuous) and logistic (binary) regression models, accounting for intra-class correlation within health facilities. We will create a composite score for women’s experiences of SDMC which will treated as outcome for pre-post comparison using linear regression. Depending on distribution of the variable, we will consider dichotomising it to see pre-post intervention changes in prevalence of SDMC experiences using logistic regression. Paired t-test (for continuous) and McNemars test (for binary) will be used to observe change in knowledge and attitudes of health facility staff before and after training. Stata version 16.1 (StataCorp LP, Texas, United States) will be used for all analyses, and p-values of 0.05 will be considered statistically significant.

For the qualitative enquires of formative research, we will use bottle-neck analysis approach to identify prevalent issues that impedes provision of SDMC in health facilities, and also determine the opportunties that can be leverage to promote SDMC. These findings will inform the development of intervention package. The qualitative data to be collected post-intervention, will be analysed to understand feasibility and acceptability of SDMC intervention, and related barriers and facilitators of implementation. We will also analyse suggestions of study participants to make improvements in the intervention package.

The researchers will thoroughly review all of the transcripts several times to identify predetermined and emerging themes from the data as per the objectives. Audio-recording of the IDIs will be transcribed verbatim and translated from Urdu/local language into English. These transcripts will be used for detailed analysis. The data will be coded and thematically analysed using QSR NVivo 11 software for Windows.

*Covariates*. The adjustment for potential confounders will be primarily required to see changes in women’s experiences of SDMC. The analysis will be adjusted for following covariates: women’s age, ethnicity, level of education, employment status, level of empowerment, socio-economic status, functional disability, and anxiety or depression. These characteristics have found to be associated with disrespectful and abusive care at health facilities [5].

The progress and success of this early-phase research will be monitored and evaluated based on key indicators presented in Table 1. The immediate outputs will be development of a training manual for health facility staff and their training which will lead to improved knowledge and positive attitude towards regarding SDMC. Simultaneously, changes in the routine system will take place to create opportunities and encourage them to practice new behaviours. Post-intervention, perceived feasibility, penetration and challenges will be assessed that inform success of the intervention.

**Table 1 pone.0263635.t001:** List of input, process, intermediary and outcome indicators.

Level of indicator	Indicators	Instrument/ means of verification	Time	Objectives
Inputs	SDMC training handbook finalised based on the feedback of feasibility testing	Training manual	Inception phase	Objective 1
	Structural changes incorporated within health system	Systemic changes	Inception phase	Objective 1
	Number of participants trained on SDMC	Training reports	Inception phase	Objective 2
Intermediate outcomes	Mean score of service providers’ knowledge of SDMC	Knowledge questionnaire	Pre-post training test	Objective 2
	Mean score of service providers’ attitude towards SDMC	Attitude questionnaire	Pre-post training test	Objective 2
Implementation/ process outcomes	Penetration of SDMC across cadre (qualitative)	in-depth interview	Endline	Objective 2
	Feasibility and acceptability of SDMC package (qualitative)	in-depth interview	Endline	Objective 2
	Barriers and facilitators to implementation of SDMC (qualitative)	in-depth interview	Endline	Objective 2
Service outcomes	Mean score of women’s experiences of inclusive, supportive and dignified maternity care	Structured SDMC questionnaire	Baseline and endline	Objective 2

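### The women's survey is sized on a 0–40 mistreatment score, but the analysis section and Table 1 name only an SDMC-experience composite, so the stated 90% power is not shown to apply to the outcome analysed

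*Protocol article*

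**What the plan says.** Three places in the protocol article describe the women's outcome.

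- **Women's experiences, Sample size calculation.** The outcome is a mistreatment score: "Mean score mistreatment was considered as key outcomes which is taken from a background study in similar setting". The background study "yielded a mean score of 25 (score range 0 to 40"). The target is a "2.5-units decrease (or 10% reduction) in the mean score of mistreatment", "with standard deviation of 6 [34], 90% power, 5% level of significance, 2 design effect", and "10% lost-to-follow-up (LTFU) and/or non-response". The mean and SD are cited to reference 34. The result is given as a total of 308 postpartum women.
- **Women's experiences, Data analysis.** A composite is to be created for women's "experiences of SDMC which will treated as outcome for pre-post comparison using linear regression". Depending on its distribution, it may be dichotomised and analysed by logistic regression.
- **Table 1, Service outcomes.** The only service outcome is the mean score of women's "experiences of inclusive, supportive and dignified maternity care", measured at baseline and endline with a structured SDMC questionnaire.

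On the instrument, the Quantitative methods paragraph says that a recently published "structured questionnaire on mistreatment during childbirth will be contextually adapted and used for these pre-post assessments [33"]. This is a different citation number from the source of the mean and SD.

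The same paragraph enrols independent groups of women at baseline and endline. The Discussion says that the study will not give robust evidence on effectiveness and that change in women's experiences is not the primary objective.

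**The concern.** A sample size calculation supports a power claim only for the variable whose SD and target difference went into it. Here those inputs belong to a mistreatment score on a stated scale. The variable to be regressed is named differently, has yet to be built, and has no stated scale, SD or target change. It may also become binary, and a 2.5-unit difference with SD 6 says nothing about a difference in proportions.

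This is more than detail left to an analysis plan. The article makes a definite power claim for one named outcome, and then names another in its analysis section and indicator table. If the two are not the same score, a reader cannot tell what change the survey could detect. A null or a significant pre-post result would then be hard to interpret. It would also be unclear whether the mistreatment mean, the composite or its binary form was meant as the main comparison.

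**Working it through.** **1. The three places side by side**

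| Place | Outcome | Scale, SD, target change |
|---|---|---|
| Sample size calculation | Mean mistreatment score (reference 34) | 0–40, mean 25, SD 6, fall of 2.5 |
| Data analysis | SDMC-experience composite, possibly dichotomised | none given |
| Table 1 | Mean score of inclusive, supportive and dignified care | none given |

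No sentence equates the first row with the other two.

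**2. The plan's own figure**

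Inputs from the Sample size calculation: difference 2.5, SD 6, power 90%, alpha 5%, design effect 2, loss 10%. Assumptions, because the article does not state them: a two-sided test and equal rounds.

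- Standardised difference: 2.5/6 = 0.417.
- Per round before inflation: 2 × (1.960 + 1.2816)² / 0.417² = 121.04, rounded up to 122.
- Design effect: 122 × 2 = 244.
- Loss: 244/0.9 = 271.1, rounded up to 272 per round, or 544 in total.

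The stated 308 is not reproduced. Without the design effect the total is 272, which is also not 308. No variant tried at 90% power comes within 3% of 308. The nearest variant was a one-sided test at 80% power with loss added as 10%. It gives 317 and contradicts the stated power.

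**3. What 308 delivers, whatever the outcome**

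*If 308 is the total:*

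- Effective n per round: 154 × 0.9/2 = 69.3.
- Detectable at 90% power: 3.2415 × √(2/69.3) = 0.551 SD. On the mistreatment scale this is 0.551 × 6 = 3.3 units.
- Power at 0.417 SD: Φ(0.417 × √(69.3/2) − 1.96) = Φ(0.49) ≈ 0.69.

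*If 308 is per round:*

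- Effective n per round: 308 × 0.9/2 = 138.6.
- Detectable at 90% power: 3.2415 × √(2/138.6) = 0.389 SD.
- Power at 0.417 SD: Φ(0.417 × √(138.6/2) − 1.96) = Φ(1.51) ≈ 0.93.

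**4. Sensitivity to the unknown standardised change in the composite**

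The documents give no value, so the effects below are assumed. The other settings are as in step 2.

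| Assumed effect (SD) | Total for 90% power | Power, 308 in total | Power, 308 per round |
|---|---|---|---|
| 0.25 | 1498 | 31% | 55% |
| 0.30 | 1040 | 42% | 71% |
| 0.35 | 766 | 54% | 83% |
| 0.417 | 544 | 69% | 93% |
| 0.50 | 378 | 84% | 99% |

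Power carries over from the mistreatment score to the composite only if the composite's standardised change is similar. The article gives no basis for judging that.

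**The case against.** The strongest reply is that there may be only one score. The Quantitative methods paragraph describes a single instrument for women's experience of SDMC, and that instrument is an adapted mistreatment questionnaire. The formative work is meant to shape structured tools for the same purpose, so the SDMC questionnaire in Table 1 is most naturally that adapted tool. The composite could be the mistreatment score under the programme's label. This stands as a possibility. It is why the point is that the power is not shown to apply.

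Three stronger readings are tempting, and the documents do not support them.

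- *References 33 and 34 are different instruments.* Two citation numbers do not show that. Whether the background study used the same tool cannot be settled from the article.
- *Mistreatment is never analysed.* The sample size paragraph plans estimates of the prevalence of mistreatment types and of the intervention effect on each. What lacks a stated analysis is the overall mean score used for sizing.
- *The mismatch causes the 0.55 SD figure.* It does not. That figure follows from 308 in total and would hold equally for the mistreatment score.

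It is also fair to say that the Data analysis section and Table 1 agree with each other, that the calculation was offered to get a feel for the numbers needed, and that this is a pilot. These points lower the stakes. They do not remove the conflict, because the article still claims 90% power, plans regression with a 0.05 threshold, and says in the Abstract that women's experiences will inform the success of the intervention.

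**Conclusion.** The concern holds in a limited form. The outcome used for sizing and the outcome named for analysis are not tied together. The analysed composite has no SD or target change, so the 90% power claim has no stated basis for it. A reader might go further and infer that the power figure is wrong for the composite. That is not proven, since the scores may overlap or coincide and a standardised change near 0.417 would carry the calculation over.

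The size of any power loss from the mismatch cannot be fixed. Over assumed effects of 0.25 to 0.50 SD, power runs from 31% to 84% for 308 in total, and from 55% to 99% for 308 per round.

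Separately, if 308 is the total, as the wording says, the survey has about 69% power for the article's own mistreatment target, not 90%. This rests on a two-sided 5% test, equal rounds, design effect 2 and 10% loss. Read as per round, power is about 93%.

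The point is worth correcting, but its consequence is limited by the disclaimer in the Discussion.

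**What to change.** Name one main service outcome, in the same words, in the Sample size calculation, the Data analysis section and Table 1.

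- If the composite is the 0–40 mistreatment score, say so.
- If it is not, there are two options:
  - make the mistreatment score the main analysed outcome, with the SDMC composite and any binary version secondary, provided the adapted questionnaire can yield that score; or
  - keep the continuous composite as main, state its detectable change in SD units, and check its SD from the baseline round before endline begins.

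In either case, state whether 308 is the total or the number per round, and restate the power or detectable difference to match: about 0.55 SD at 90% power for a total of 308, or about 0.39 SD for 308 per round.

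The cost is wording in three places and, for the composite, a look at baseline data that are already planned. The mistreatment-score option also needs a check that the adapted tool keeps the required items. More women would be needed only if the sponsor wants 90% power for 0.417 SD and 308 is the total. That would take about 544.

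### The total of 308 women does not follow from the stated inputs: they need about 544, and 308 in total gives about 69% power rather than 90%

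*Protocol article*

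**What the plan says.** The relevant text is in the protocol article under Women's experiences.

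- Design (Quantitative methods): "two independent group of women will be enrolled in baseline and endline". The pre-post comparison of women is therefore between two unpaired samples.
- Required number (Sample size calculation): "A total of 308 postpartum women will be required to detect a statistical difference of 2.5-units decrease (or 10% reduction", that is, from a mean of 25 to 22.5.
- Inputs (same paragraph): "with standard deviation of 6 [34], 90% power, 5% level of significance, 2 design effect, and 10% lost-to-follow-up (LTFU" or non-response.
- Use of the number: the authors go ahead with 308 because "it gives sufficient precision to perform range of additional analysis such as estimation of prevalence of different types of mistreatment", and also the intervention's effect on each type.

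The paragraph does not say whether 308 covers one survey round or both, beyond the word total. It does not say whether the 5% level is one- or two-sided.

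**The concern.** Apart from sidedness and the split between rounds, every input is printed, so the figure can be checked directly. It does not come out. The gap is too large to be rounding or a choice between standard formulas.

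Three things are at stake.

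- **Power.** If 308 is the total, the chance of missing the fall the survey was sized for is about 31%, not 10%. A null result read as coming from a study with 90% power would be over-interpreted. The Discussion makes the step to a cluster randomised trial depend partly on the package's potential to improve mothers' experiences.
- **Recruitment.** Under Sampling strategy, women are invited until the target is reached and the sample is shared across facilities by caseload, so 308 is an operational quota. Reading it as one round or as both changes enrolment twofold.
- **The precision claim.** The statement about individual mistreatment types rests on the same number and has no figure behind it.

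**Working it through.** **Inputs, all from Sample size calculation unless noted**

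- Two independent groups (Quantitative methods); equal rounds assumed
- Difference 2.5, SD 6
- 5% level, taken as two-sided (assumption; one-sided is shown below)
- Power 90%, so z = 1.960 + 1.2816
- Design effect 2, loss 10%

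**Attempt to reproduce 308**

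1. Per round, before inflation: 2 × (1.960 + 1.2816)² × 6² / 2.5² = 121.05, rounded up to 122.
2. Design effect: 122 × 2 = 244.
3. Loss: 244 / 0.9 = 271.1, rounded up to 272 per round.
4. Both rounds: 2 × 272 = **544**. The stated figure is 308.

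**Variants**

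| Variant | Per round | Total |
|---|---|---|
| As stated, two-sided | 272 | 544 |
| Loss applied as × 1.1 | 269 | 538 |
| One-sided 5% | 220 | 440 |
| Two-sided, 80% power | 203 | 406 |
| Two-sided, design effect left out | 136 | 272 |
| One-sided, 80% power | 160 | 320 |

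None gives 308. The nearest total, one-sided with 80% power, contradicts the stated 90%.

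**Power of 308 in total**

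- 308 / 2 = 154 per round; 154 × 0.9 = 138.6 complete; 138.6 / 2 = 69.3 effective.
- 2.5 / (6 × √(2/69.3)) = 2.453. Power = Φ(2.453 − 1.960) = **0.689**.
- One-sided: 0.790. Two-sided with no loss at all (77 effective): 0.734.
- Difference detectable with 90% power: (1.960 + 1.2816) × 6 × √(2/69.3) = 3.30 units, which is 3.30/25 = 13% of the baseline mean. With 80% power it is 2.86 units.
- Leaving out the design effect (138.6 effective) raises power to 0.934. The largest design effect that 308 in total can carry at 90% power is 138.6 / 121.05 = 1.14.

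**Power of 308 per round (616 in total)**

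- 308 × 0.9 / 2 = 138.6 effective.
- 2.5 / (6 × √(2/138.6)) = 3.469. Power = Φ(3.469 − 1.960) = **0.934**.

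**Precision by mistreatment type**

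Assumptions: prevalence 50% and design effect 2 for every type. The first two rows are 95% CI half-widths.

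| Quantity | 308 in total | 308 per round |
|---|---|---|
| One round: 1.96 × √(0.25/n) | ±11.8 points | ±8.3 points |
| Change: 1.96 × √(0.50/n) | ±16.6 points | ±11.8 points |
| Fall from 50% detectable at 90% power | about 26 points | about 19 points |

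Here n is 69.3 or 138.6. The last row solves d = 3.2416 × √((0.25 + (0.5 − d)(0.5 + d))/n). At the 69% to 78% that Country context cites for some types, the one-round half-widths with 308 in total are somewhat smaller: 1.96 × √(0.69 × 0.31/69.3) = 10.9 points and 1.96 × √(0.78 × 0.22/69.3) = 9.8 points.

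**The case against.** The strongest reply is that 308 may be a per-round quota. Sampling strategy speaks of recruiting within a data collection period until the target is met, which suits a quota for one round. The authors also say they chose to proceed with 308 after looking at several effect sizes, so a per-round number above the minimum of 272 is conceivable. Power would then be about 93% and the stated 90% would be met. This stands as a possible intention, and the fix allows for it. It does not stand as a reading of the text, which calls 308 a total and presents it as the number required by inputs that give 272 per round.

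Second, sidedness is assumed here. With a one-sided 5% test the chance of missing the target change is about 21% rather than 31%. That narrows the shortfall but does not remove it.

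Third, this is feasibility work. The Discussion says robust evidence of effectiveness is not expected and that change in women's experiences is not the primary objective. That is a fair argument for a lower severity. But the protocol chose to power this comparison, calls the mistreatment score a key outcome, and plans regression at the 0.05 level. A stated power that the design does not have still needs correcting.

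Fourth, the precision claim names no target, so whether about ±12 points per round is sufficient is a matter of judgement. That stands. The point is only that the claim should carry its figures.

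**Conclusion.** The concern holds. On the printed inputs, with two equal independent rounds and a two-sided 5% test, 544 women are needed. The stated total of 308 gives 68.9% power for a 2.5-unit fall and 90% power only for a fall of about 3.3 units. If 308 is per round, power is 93.4% and the comparison is adequately sized, but the wording is then wrong and the number is still not the one the inputs give. No standard variant yields 308 at 90% power with the stated design effect. Because the outcome is not the primary objective, the harm lies in a misstated power and an ambiguous quota rather than in a design that cannot serve its main purpose.

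**What to change.** Say which of the two is meant, and give the matching power and the sidedness:

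- If 308 is the total: 154 women per round, about 69% power (two-sided 5%) for a 2.5-unit fall, and 90% power for a fall of about 3.3 units.
- If 308 is per round: 308 per round, 616 in total, about 93% power for a 2.5-unit fall.

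Replace the claim of sufficient precision with the expected half-widths, with their assumptions. At 50% prevalence these are about ±12 points per round and ±17 for the change if 308 is the total, or about ±8 and ±12 if it is per round. Presenting results by mistreatment type as estimates with confidence intervals rather than as tests would fit these widths, but it is a preference and not part of the correction.

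The cost is wording only. If 308 is the total, the stated power becomes less favourable. No additional enrolment is requested.

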### Objective 2: Implement and test the feasibility of the intervention model for its content and operationalisation in public health facilities

#### Phase 3: Implementation and testing

The third phase of HCD fall within the scope of second study objective. In phase three, the finalisation of prototype will be followed by pilot testing in real-life settings over a period of three months. It is important to note that this implementation is will be considered pilot as the field learnings will be fed back into design of intervention package.

*Evaluation design*. A mixed-method, pre-post design will be used to test feasibility of the intervention prototype.

*Study settings*. The study will be implemented at six public health facilities–with three facilities in each Thatta and Sujawal districts of southern Sindh province, Pakistan. These contagious districts are located approximately 100 kilometres away from megacity, Karachi. Each district has a population of approximately 0.8 million inhabitants, with 82% of them residing in rural areas [31] and just over half (52.3%) of the population belong to the poorest wealth quintile relative to the Sindh province (South of Pakistan) [32]. Only 15.8% of the total births take place in public sector health facility [32].

*Study population*. The primary target-audiences will be women in childbirth and service providers (clinical and non-clinical staff) of the labour room / maternity wards.

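### With six facilities, the common large-sample forms of the planned facility-adjusted regressions reject too often; base the interval on the six facility-level changes

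*Protocol article*

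**What the plan says.** Under Phase 3, Study settings: "The study will be implemented at six public health facilities", three in each of two districts. The evaluation is pre-post with no concurrent control ("A mixed-method, pre-post design will be used to test feasibility of the intervention prototype"), and for the women's survey "two independent group of women will be enrolled in baseline and endline". Each facility therefore contributes a different set of women to each round.

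Under Sampling strategy, the sample is shared out by historical caseload, so facility samples will be unequal wherever volumes differ.

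Under Data analysis, the models are "multivariable linear (continuous) and logistic (binary) regression models, accounting for intra-class correlation within health facilities", and "p-values of 0.05 will be considered statistically significant". Eight covariates are listed under Covariates. The text does not say whether the intra-class correlation is handled by robust standard errors, a random intercept, generalised estimating equations or facility effects. It neither gives nor rules out a small-sample correction.

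The sample-size paragraph targets a "2.5-units decrease (or 10% reduction) in the mean score of mistreatment" with "standard deviation of 6 [34], 90% power, 5% level of significance, 2 design effect, and 10% lost-to-follow-up (LTFU) and/or non-response". The Discussion states that the study will not give robust evidence of a change in women's experiences.

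**The concern.** The pre-post contrast is replicated over six facilities. If facilities change by different amounts, that variation is estimated from six differences, which leaves 5 degrees of freedom however many women are interviewed. Large-sample cluster-robust inference relies on many clusters. A facility intercept alone removes stable differences between facilities but not differences in how they change.

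Such differences are plausible here, because the intervention works through each ward's own team leadership, performance review and audit feedback. The sample size also applies a design effect of 2 to a comparison made within the same facilities. That inflation would not be needed if facility effects simply cancelled.

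At stake is whether a chance shift between rounds is reported as a significant improvement. The abstract lets women's experiences inform the judgement of success. The Discussion makes the potential to improve those experiences part of the basis for a later cluster-randomised trial.

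**Working it through.** **1. The plan's own figure.** Two-sided 5% (sidedness is not stated), 90% power, SD 6, difference 2.5:

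n per round = 2 × (1.960 + 1.282)² × 6² / 2.5² ≈ 121, rounded up to 122. With design effect 2, this is 244. With 10% loss, 244 / 0.9 = 271.1, so 272 per round; for both rounds, 488 / 0.9 = 542.2, so 543.

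The article's figure ("A total of 308 postpartum women will be required to detect a statistical difference") matches neither. That is a separate matter. Because the text does not settle whether 308 is per round or in total, both readings are carried below.

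**2. Degrees of freedom.** Six differences give 6 − 1 = 5 df. The 97.5% point is 2.571 for t(5) against 1.960 for the normal, a ratio of 1.31. If a statistic truly follows t(5) but is compared with 1.960, it rejects 10.7% of the time and the nominal 95% interval covers 89.3%.

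**3. Intra-class correlation.** None is given. Solving 1 + (m − 1) × ICC = 2 gives ICC = 1 / (m − 1):
- 154 women per round: m = 154 / 6 = 25.7, ICC = 0.041.
- 308 women per round: m = 308 / 6 = 51.3, ICC = 0.020.

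**4. Simulation under no change.** Six facilities, two rounds with different women, ICC as in step 3, 2,000 data sets per scenario. The Monte Carlo standard error at 5% is √(0.05 × 0.95 / 2000) = 0.5 percentage points. The unequal shares 8:5:3:2:1:1 are an assumption. Rejection at nominal 5%:

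| Analysis | Equal facilities | Unequal facilities |
|---|---|---|
| Cluster-robust, normal reference, linear | 10–12% | 13–18% |
| Cluster-robust, normal reference, logistic | 10–12% | 14–18% |
| Cluster-robust, t(5), linear | about 4–5% | about 6–11% |

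Facility effects with an ordinary standard error and normal reference (fixed facility effects as a stand-in for a random intercept), equal and unequal facilities together:

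| Share of facility variance that is facility-by-round | Rejection |
|---|---|
| None | 4–6% |
| Half | 11–16% |
| All | 16–23% |

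With a smaller share than half, the rate falls to about 7%. The six facility-level differences on t(5) reject 3–8% across scenarios, mostly near 5%, for means and for proportions.

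**5. Power on 5 df.** Standard error = 6 × √(2 / n_eff), noncentrality = 2.5 / standard error, with the design effect of 2 applied in full and 10% loss:

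| Case | n_eff per round | Noncentrality | Normal reference | t(5) |
|---|---|---|---|---|
| Planned 90% | 122 | 3.25 | 90% | 74% |
| 308 per round | 308 × 0.9 / 2 = 138.6 | 3.47 | 93% | 79% |
| 308 in total | 154 × 0.9 / 2 = 69.3 | 2.45 | 69% | 51% |

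**The case against.** The strongest reply is that the criticised test is not in the document. Accounting for intra-class correlation is compatible with t on 5 df, with a two-stage analysis, or with a corrected mixed model, and an article may leave that choice to the full protocol or analysis plan. This stands. A reader might infer that the plan commits to normal-reference inference and so contains an error, but the text does not support that.

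A reader might also infer that intervals must be too narrow unless 5 df are used. That is not general either. Every facility is in both rounds, so a stable facility effect cancels, and a facility-intercept model then rejects at about 5% with a normal reference. The excess depends on facility-by-round variation, whose size the article does not give. Nor is a t(5) reference for robust standard errors a full remedy when facilities are markedly unequal.

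The power losses in step 5 assume no cancellation. If 0.5 to 0.8 of the facility variance is shared between rounds, power on t(5) is 63–73% for 308 in total and 89–95% for 308 per round. The low starting point for 308 in total is a sample-size question, not a degrees-of-freedom one.

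Finally, the Discussion says that change in women's experiences is not the primary objective, and it sets no significance criterion for moving to a trial. That limits the consequence. Still, the article tests at 0.05 and lets these results inform success.

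**Conclusion.** The point holds as a recommended improvement, not as a demonstrated error. The class of regression that the plan states, applied in its usual large-sample form to six facilities, would reject about 10–18% of the time (cluster-robust) or about 7–23% (facility intercept, where change varies between facilities) at a nominal 5%. An analysis of the six facility-level differences stays mostly near 5%.

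These rates assume an ICC calibrated to the plan's design effect of 2, assumed unequal shares where sizes differ, and, for the facility-intercept figure, some facility-by-round variation. The 74% power figure for a design with a nominal 90% holds only if the design effect applies in full to the pre-post contrast. The study's disclaimer of robust effectiveness evidence keeps the consequence moderate.

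**What to change.** State in the analysis plan that the confidence interval for the change in women's experiences rests on the six covariate-adjusted facility-level pre-post differences, with t on 5 df. For binary outcomes, use differences in facility proportions. For the continuous score, a mixed model with facility and facility-by-round effects and a small-sample df correction such as Kenward–Roger is an acceptable alternative. That correction belongs to linear mixed models and does not carry over directly to the logistic outcomes. Report the estimate with its interval as the main result, ahead of the p-value.

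Design, recruitment and data collection do not change. The cost is some extra analysis work and intervals up to about 31% wider through the critical value, with the power loss shown above, which is smaller if facility effects partly cancel. A simple average of six differences also weights facilities equally rather than by number of women. The plan should say that this is the intended estimate; any further loss of precision from equal weighting was not quantified here.
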